### Assessed variables

2.2

A full list of the variables collected in the cross-sectional study is reported in Table 1. The clinical research team will collect the information of participants by consulting the patient's electronic/paper medical records and through validated questionnaires and structured interviews involving mothers at the enrollment. Structured interview characteristics are reported in Supplementary Table S1.

**Table 1 T1:** List of variables collected in the cross-sectional study.

Variables	Methods	Sample
Demographic data	Structured interview	M
	Structured interview	C/A
Medical history and medication use	Structured interview	M
	Structured interview	C/A
Anthropometric parameters	Height, weight, BMI; waist circumference, direct measurement (27–29)	M
	Height, length or height; waist circumference, direct measurement (30, 31) Percentile of BMI, percentile of waist circumference, AR, calculated (30, 31)	C/A
Dietary pattern	Structured interview	M
Mediterranean Diet Adherence	Questionnaire MEDI LITE Score (32, 33)	M
	Questionnaire KIDMED (Diet Quality Index for Children and Adolescents) (34)	C/A
Physical activity level	International Physical Activity Questionnaire (IPAQ-SF; shortform) (35–37)	M
	Structured interview for children (38, 39)	C
	Questionnaire International Physical Activity Questionnaire for Adolescents (IPAQ-A) (40, 41)	A
Screen time and sedentary behaviour	Structured interview (38, 39)	C/A
Smoking habits and alcohol consumption	Structured interview (42)	M
	Structured interview (42)	A
Sleep	Questionnaire Pittsburgh Sleep Quality Index (PSQI) (43, 44)	M
	Structured interview (39, 45)	C/A
Socio-economic status	Calculated	M
Family relationships	Questionnaire Child-Parent relationship scale—Short Form (CPRS-SF) (46, 47)	M
Social capital	Questionnaire Personal Social Capital Scale (PSCS-8) (48)	M
Neighborhood food environment characteristics	Mapping and Spatial analysis; Structured interview	M
Social participations	Structured interview	M

M, mother; C, Children; A, Adolescent; BMI, Body Mass Index; AR, Adiposity Rebound.

#### Socio-demographic variables

Socio-demographic features will be collected with a structured interview. In detail, mother's age, marital status (marry/cohabitant, divorced/separated, widow, single), ethnicity (Caucasian, Black, Medioriental, Asiatic, Hispanic), nationality, education level (none, elementary, middle school, high school, degree), number of people in the household, number of children, number of years in Italy (if not Italian), residential address.

#### Economic, social, cultural and environmental variables

Socio-economic and socio-cultural characteristics will be collected through structured interviews. Information on household income, job/work and housing status (surface; owned, rented, sub-rented, social housing, guest, other) will be collected to detect socio-economic status.

Family relationships will be derived from the Child-Parent relationship scale-Short Form (CPRS-SF), a 15-item questionnaire assessing mothers' perception of their relationship with their son or daughter (46, 47). The Personal Social Capital Scale (PSCS-8) short form will be used to assess maternal durable and trustworthy social connections (48). Maternal social participation will be investigated through a structured interview to explore type (i.e., religious, recreational, cultural and, political) and frequency of activities.

Environmental factors that may influence nutrition, physical activity and lifestyle will be considered through the collection of geo-data on the characteristics of the food environment (e.g., the built environment, proximity to recreational/sport facilities, parks) and the transport infrastructure (e.g., walkability) (35, 49).

#### Medical history

Maternal and children/adolescent medical history will be explored through a structured interview (i.e., medical issues which includes all diseases and illnesses currently being treated and those which have had any residual effects on the mother and children/adolescent's health, medication history, surgical history and family medical history with potential indicators of predisposition to disease).

#### Anthropometric variables

Anthropometric measures of mothers will be collected using standardised procedures (27–29), weight (kg) will be measured with a calibrated weighing scale wearing underpants only (accuracy ± 100 g), height (cm) by a fixed stadiometer with a vertical backboard and a moveable headboard (accuracy ± 1 mm) and waist circumference (cm) will be measured with an elastic tape.

Height (cm) and weight (kg) will be collected also for children/adolescents. Briefly, standing height will be measured as previously described and according to standard procedures (28, 29). Recumbent length will be assessed for children who still are unable to stand up (29). Body weight of unclothed children/adolescents will be collected using a balanced weight scale (accuracy ± 100 g), following standardised procedures (29). WHO child growth standards will be used to diagnose overweight (BMI Z-score >1) or obesity (BMI Z-score ≥2) (50). Infant growth curves from the paediatric booklet will be requested to evaluate the time (year) of the adiposity rebound. The presence of an early adiposity rebound (EAR) will be identified when the lowest BMI during child growth occurs at an age <5 years old (30, 31) and children/adolescents will be categorised into early or non-early adiposity rebound (AR). Waist circumference (cm) will be collected in children/adolescents using standardised procedures (29).

#### Lifestyle variables

##### Mediterranean dietary pattern adherence, self-perception of the current diet and eating attitude

For mothers, Mediterranean dietary adherence will be explored using the 9-item MEDI-LITE questionnaire (32, 33). The questionnaire investigates the frequency of consumption of nine classes of food (i) fruit, (ii) vegetables, (iii) cereal grains, (iv) legumes, (v) fish and fish products, (vi) meat and meat products, (vii) dairy products, (viii) alcohol intake, and (ix) olive oil. The score obtained from the questionnaire ranges from 0 to 18, where the highest value corresponds to the highest MD adherence (33). Moreover, a structured interview will be also used to evaluate self-perception of the current diet, to investigate any dietary restrictions (i.e., carbohydrates, fat, meat, fish, eggs, dairy, gluten, lactose) or consumption of traditional food/dishes.

For children, Mediterranean dietary adherence will be assessed with the KIDMED (Diet Quality Index for Children and Adolescents) questionnaire (34). The KIDMED is a 16-item tool used for the evaluation of consumption of fruit, fruit juice, vegetables, fish, pulses, cereals, nuts, olive oil and yoghurts or cheese. KIDMED also explores fast-foods, commercial bakery goods and pastries, sweets and candy consumption, as well as eating behaviours (i.e., skipping breakfast). In addition, for children, a structured interview of two items will assess the endorsement of any of the following binge eating symptoms (i) sneaking, hiding, or hoarding food, (ii) eating in the absence of hunger. These questions have been selected in previous trials with the aim to examine the prevalence of overeating symptoms in overweight or obesity affected children and adolescents (51–53).

#### Physical activity

Maternal physical activity will be assessed by the short form (7 items) of a validated country-language-specific questionnaire [International Physical Activity Questionnaire (IPAQ—SF)] (36). The questionnaire provides an estimate of the metabolic equivalent of task (MET-min) per week, which is calculated as follows: METs = MET level ×  minutes of activity × events per week. Physical activity level will be classified according to METs into sedentary (total METs <699), moderate (total METs between 700 and 2,519), and high (total METs >2,520) (37, 54).

For children aged 2–14 years old, physical activity habits will be explored through a structured interview, differentiating questions according to the different age groups (3–4 years, 5–14 years) as suggested by WHO guidelines for physical activity (38, 39).

For adolescents aged 15–17 years old, the Italian version of the International Physical Activity Questionnaire for Adolescents (IPAQ-A) will be used to investigate time spent in physical activities in different settings (i) school-related physical activity, (ii) housework, house maintenance and gardening, (iii) transportation, (iv) recreation, sport, and leisure-time physical activity (40, 41). The quantity of physical activity will be calculated by multiplying the energy expenditure required (MET) and the amount of time spent (min) in a week for each activity. Moderate intensity will be weighed in absolute terms as 4 METs, vigorous intensity defined as 8 METs and walking as 3.3 MET.

Children's sedentary screen time behaviours will be also assessed through a structured interview, differentiating the use of screens (i.e., TV, other devices such as smartphone, computer, tablet, touch screen, and game console) at home and school for both weekdays and weekends. Total screen exposure results will be compared to WHO guidelines (38, 39).

#### Alcohol consumption and smoking habit

For mothers and adolescents (12–18 years old) interviews will be used to assess smoking habits and alcohol intake. Concerning smoking habits usage of traditional tobacco cigarettes (manufactured or hand-rolled cigarettes), electronic cigarettes or heated tobacco products (HTP) will be evaluated. Participants will be then categorised as follows (i) never smoker, (ii) past smoker (i.e., current non-smoker), (iii) current smoker.

According to the frequency of alcohol intake, the respondents will be segmented in three categories (i) abstainers [i.e., subjects who do not drink alcohol, zero Units of Alcohol (U.A.)], (ii) occasional drinkers (i.e., subjects who drink less than 1 U.A./week), (iii) daily drinkers (i.e., subjects who regularly drink alcohol, more than 1 U.A./week). According to the Italian “Linee Guida per una sana alimentazione” (42) 1 U.A. equals 12 g of pure alcohol contained in a small glass of red/white/rosé wine (125 ml, alcohol by volume 12%), one can of double malt beer (330 ml, ABV 4.6%), or a small shot of hard liquor (40 ml, ABV 40%).

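### The alcohol classes leave out a respondent at exactly one unit a week and call everyone above one unit a week a daily drinker

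*Protocol article*

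**What the plan says.** Section 2.2, under the heading on alcohol and smoking, applies to mothers and to adolescents aged 12–18. It states the basis of the grouping: "According to the frequency of alcohol intake, the respondents will be segmented in three categories". The three classes are:

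- abstainers: "subjects who do not drink alcohol, zero Units of Alcohol (U.A"
- "occasional drinkers (i.e., subjects who drink less than 1 U.A./week"
- "daily drinkers (i.e., subjects who regularly drink alcohol, more than 1 U.A./week"

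The same paragraph fixes the unit: "1 U.A. equals 12 g of pure alcohol contained in a small glass of red/white/rosé wine", or one can of beer, or one small shot of spirits.

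Under Physical activity in the same section, mothers' weekly totals are classed as "sedentary (total METs <699), moderate (total METs between 700 and 2,519), and high (total METs >2,520".

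Section 2.4 (Data analysis) says that enrolled subjects will be described on all collected variables, so these classes can be expected in the descriptive results. Nothing elsewhere in the article assigns the boundary values or redefines the word daily.

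**The concern.** A classification rule should give every possible answer exactly one class, and each class name should describe the people in it. The alcohol rule fails on both counts.

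The omitted value is not an odd decimal. It is the smallest whole number of drinks per week above zero. Whoever codes such an answer has to choose a class ad hoc, and different coders may choose differently.

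The name of the top class disagrees with its own cut-off. It speaks of days while the cut-off is a quantity per week, and the sentence introducing the classes says that they rest on frequency. A reader of the results would take a percentage of daily drinkers, including one among adolescents, at face value. What is at stake is a descriptive result that says something other than what was measured.

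**Working it through.** The plan states no computed figure on this point, so there is none to reproduce. The check is whether the printed intervals cover every value and whether the label fits its cut-off.

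**1. Coverage of the alcohol classes.** Let x be units per week, with cut-offs from the alcohol paragraph of section 2.2.

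| Class | Values of x |
|---|---|
| Abstainer | x = 0 |
| Occasional | 0 < x < 1 |
| Daily | x > 1 |

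The union is all x ≥ 0 except x = 1. No two classes overlap. The single missing point is one drink a week.

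**2. Is one unit really one drink?** Taking an ethanol density of 0.789 g/ml (an assumption; the article gives none):

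- wine: 125 × 0.12 × 0.789 = 11.8 g
- beer: 330 × 0.046 × 0.789 = 12.0 g
- spirits: 40 × 0.40 × 0.789 = 12.6 g

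All are close to the stated 12 g. The unit is internally consistent, and an answer of one glass a week does fall on the missing point.

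**3. Label against cut-off.** Three patterns of drinking, all placed in the top class:

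| Pattern | U.A. per week | Drinks daily? |
|---|---|---|
| One unit on each of 2 days | 2 × 1 = 2 | No |
| Seven units on one evening | 1 × 7 = 7 | No |
| One third of a unit every day | 7 × 1/3 ≈ 2.3 | Yes |

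The weekly amount does not tell daily drinkers from others. Raising the cut-off would not change that: at 7 U.A. a week the single-evening drinker would be in and the true daily drinker of the third row would be out. The name needs drinking days, or it needs to change.

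**4. Maternal activity.** The printed classes omit totals from 699 up to but not including 700, and totals above 2,519 up to and including 2,520. The score is "METs = MET level × minutes of activity × events per week". The weights used here (walking 3.3, moderate 4, vigorous 8) are stated for the adolescent questionnaire and are assumed for mothers. Some totals that fall in the gaps:

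- 45 min vigorous on 7 days: 8 × 45 × 7 = 2,520
- 90 min moderate on 7 days: 4 × 90 × 7 = 2,520
- 30 min moderate on 5 days plus 10 min walking on 3 days: 4 × 30 × 5 + 3.3 × 10 × 3 = 600 + 99 = 699

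For scale, each of the three intensities was given 64 options: none, or one of 9 session lengths from 10 to 120 min on 1 to 7 days. That makes 64³ = 262,144 combinations. Of these, 147 total 699, 18 total 2,519.5 and 69 total 2,520. The sum is 234, and 234 / 262,144 = 0.09%. Applied to 269 mothers this is about 0.24 of one mother. The grid is not weighted by how often people give these answers. It shows that the gaps can be reached, not how often.

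**The case against.** The strongest reply is that these are slips of notation in covariates, not in outcomes. The article glosses the top class as people who drink regularly, so a careful reader can see what it holds. The interview itself is in Supplementary Table S1, which is not shown, and its response options may not permit an answer of exactly one unit. Exact derivation rules are often left to a fuller document.

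Part of this stands. How many respondents sit at exactly 1 U.A. a week is unknown, and the article does not say whether the label or the cut-off was the one intended. But the article did not leave the rule out. It printed a complete rule with numeric limits, and that rule omits a whole-drink answer and carries a name that its cut-off contradicts. The gloss makes the conflict visible without removing it, because a results table will carry the class name.

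For activity the objection largely succeeds. The gaps are about one MET-minute wide, most analysts would read through them, and the examples rest on weights that the article gives for another questionnaire.

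A reader might infer more than the article supports:

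- **That unclassified answers would be imputed.** Section 2.4 says that missing data will be multiply imputed. A recorded answer of 1 U.A. is not missing, and nothing says that boundary values are set to missing.
- **That the models would be weakened.** A name does not change a regression estimate. Apart from its boundary, the group above 1 U.A. a week is well defined. The article also does not say that alcohol enters the models in these classes.
- **That everyone between 1 and 7 U.A. a week is mislabelled.** This confuses amount with frequency, as the third row of the table in the working shows.

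**Conclusion.** The point holds for alcohol, as a minor error in the printed rule. Exactly 1 U.A. a week has no class, and the top class is called daily although it starts just above one drink a week. A reported share of daily drinkers among mothers and adolescents would therefore be misleading. The direction is clear to this extent: the class admits people who do not drink daily. The size cannot be given, because the article reports neither intake nor drinking days.

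For maternal activity the classes are incomplete at two boundaries, and few if any mothers would be affected. It would go too far to call those groups wrong.

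Neither variable is an outcome, so the prevalence estimates for overweight and obesity do not change. The conclusion assumes that the printed rules are the ones to be applied and that Supplementary Table S1 does not override them.

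**What to change.** Reword two derivation rules before the data are classified.

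- **Alcohol:** make the classes exhaustive and non-overlapping, for example 0; >0 to <1; and ≥1 U.A. a week. Reconcile the name of the top class with its cut-off, for example regular drinkers. Use the word daily only if the number of drinking days is recorded. Say in the introductory sentence whether the classes rest on amount or on frequency.
- **Maternal activity:** write the classes without gaps: <700; 700 to <2,520; ≥2,520 MET-min a week.

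If the interview records the amount, this costs a few words and no new data. If it records only the class, answers of exactly one unit may not be recoverable afterwards, so the change should be made while enrolment (planned to December 2025) is still open.

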#### Sleep

Pittsburgh Sleep Quality Index (PSQI) (43, 44) will be used to explore sleep quality of mothers. The PSQI is a 9-item questionnaire assessing 7 sub-dimensions of sleep (i.e., subjective sleep quality, sleep latency, sleep duration, habitual sleep efficiency, sleep disturbances, use of sleeping medication and daytime dysfunction).

For children, sleep quality will be assessed through a structured interview regarding sleep and wake-up times, sleep regularity, average number of hours of sleep per night, difficulty falling asleep and daytime sleepiness. Results will be compared to WHO guidelines (39, 45).

### Data collection and management

2.3

Participants' data will be collected in both electronic and paper form and sent by authorised study personnel to an electronic database protected by a password. Each individual participant and their data will be identified with a unique study identification number (pseudo-anonymization of data), which will prevent any direct identification. The unique identifier will be used from that point forward on all relevant documentation. The Coordinator Centre (Laboratory of Dietetics and Clinical Nutrition) will be responsible for the data storage in a locked and secured location. Laboratory of Dietetics and Clinical Nutrition and Buzzi Children's Hospital will be responsible for data entry and quality.

### Data analysis

2.4

In the cross-sectional study, sample size has been determined considering a prevalence of overweight and obesity in the target population of 17% and 4%, respectively (55). Considering a 95% level of confidence and 5% precision, 217 individuals for overweight and 52 for obesity prevalence estimates are required, for a total sample size of 269 mother-child dyads.

Enrolled subjects will be described with reference to all the collected variables by means of standard descriptive statistics. Prevalence of overweight and obesity will be estimated along with 95% confidence intervals. In order to assess the impacts of lifestyle and socio-economic, cultural, and environmental factors on overweight and obesity, logistic regression will be adopted. Overweight and obesity in children, as binary variables, will be the response in two separate logistic models, where socio-economic, cultural, and environmental factors, among all collected data, will be the independent variables. Indeed, performing different analyses according to the BMI status (overweight/obesity) will capture different health correlations, since the greater severity of overweight and obesity usually corresponds to an unhealthy lifestyle, and to a low SES (12, 21). Analyses will also be adjusted for potential confounders like age, sex or any other variable identifiable as such among the collected data.

Furthermore, if sample size allows, subgroups analysis by ethnicity (Caucasian or non-Caucasian) will be performed since it likely results in different cultural habits, impacting nutrition and other lifestyle factors (56, 57).

Missing data will be handled with multiple imputation.

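### The 52 children stated for obesity do not follow from the stated 4% prevalence (the formula gives 59 to 60), and a 5-point half-width says little about a 4% prevalence

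*Protocol article*

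**What the plan says.** Section 2.4 (Data analysis) of the protocol article bases the sample size on "a prevalence of overweight and obesity in the target population of 17% and 4%, respectively", taken from a cited source. It continues: "Considering a 95% level of confidence and 5% precision, 217 individuals for overweight and 52 for obesity prevalence estimates are required". The two numbers are then added, "for a total sample size of 269 mother-child dyads", and section 2.1 (Study setting) gives the same 269 as the enrolment figure. On the analysis side, section 2.4 says: "Prevalence of overweight and obesity will be estimated along with 95% confidence intervals". The article mentions no other prevalence, no separate precision for obesity, no finite-population correction and no allowance for losses.

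**The concern.** The two component figures should come from one formula with one confidence level and one precision, and differ only in the prevalence. The overweight figure can be reproduced from the printed inputs, but the obesity figure cannot. A reader who checks the justification will find that either the assumed prevalence or the required number is misprinted or rounded, and cannot tell which.

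The planning target for obesity raises a second question. A margin of 5 points either side of 4% is wider than the quantity itself, so meeting it says little about how well obesity prevalence will be known. Estimating that prevalence is the first stated aim of the cross-sectional study.

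At stake is whether the sample-size statement can be reproduced and whether it tells the reader what precision to expect.

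**Working it through.** **Inputs**, all from section 2.4: p = 0.17 (overweight), p = 0.04 (obesity), 95% confidence, d = 0.05. Taking the interval as two-sided and the precision as an absolute half-width is an assumption; step 1 supports it.

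**Formula:** n = z² × p(1 − p) / d², with z = 1.96 and z² = 3.8416.

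**Step 1. Reproduce the overweight figure.** 3.8416 × 0.17 × 0.83 / 0.0025 = 216.8, rounded up to 217. This matches the article and fixes the method: two-sided 95%, absolute 5 points, no correction.

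**Step 2. Same formula for obesity.** 3.8416 × 0.04 × 0.96 / 0.0025 = 59.0, so 59 to the nearest whole number or 60 if rounded up. The article has 52. The shortfall is 7 of 59 (12%) or 8 of 60 (13%), which is more than rounding.

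**Step 3. Which prevalence gives 52?** 3.8416 × 0.035 × 0.965 / 0.0025 = 51.9, rounded up to 52. Working backwards, prevalences from about 3.44% to 3.51% round up to 52.

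**Step 4. Does another method give both 217 and 52?**

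| Variant | Obesity, 4% | Overweight, 17% |
|---|---|---|
| Stated | 52 | 217 |
| z = 2 | 61.4 | 225.8 |
| One-sided 95%, or two-sided 90% | 41.6 | 152.7 |
| Finite population of about 440 | 52.1 | 145.5 |
| Wilson half-width of 5 points | 72 | 216 |
| Jeffreys | 64 | 216 |
| Clopper-Pearson | 81 | 235 |
| Agresti-Coull | 84 | 219 |

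A continuity correction gives 78 to 79 for obesity. The finite-population correction is the only variant that reaches 52, and it contradicts the stated 217. None gives both figures.

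**Step 5. The precision target.** 4% ± 5 points runs from −1% to 9%, so the half-width exceeds the prevalence.

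**Step 6. What the full sample gives.** Half-width = 1.96 × √(p(1 − p)/269):
- at 17%: 1.96 × √(0.1411/269) = 0.045, or ±4.5 points;
- at 4%: 1.96 × √(0.0384/269) = 0.023, or ±2.3 points (1.7% to 6.3%).

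The expected number of obese children is 269 × 0.04 = 10.8. The exact (Clopper-Pearson) 95% interval for 11/269 is 2.1% to 7.2%.

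**Step 7. Effect on the sum.** Adding as the article does, 217 + 59 = 276 or 217 + 60 = 277, against the stated 269.

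**The case against.** The strongest reply is that nothing in the study depends on the 52. The article describes one enrolled sample, with no separate group for obesity, so both prevalences come from the same children. At 269 the 5-point target for obesity is met more than twice over, whether the requirement is 52, 59 or 60. This stands, and it limits the point to a correction of the reported justification.

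A second reply is that the cause may be harmless: a source value near 3.5%, printed as 4%, would make 52 correct. This is plausible, but the cited source is not at hand and the article does not say so. It means that 52 cannot be called the wrong member of the pair. It does not make the printed pair consistent.

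A reader might infer more than the documents support:

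- **That the study is too small for its prevalence aim.** Step 6 shows the reverse for the stated 5-point target.
- **That the obesity target could not separate a very low prevalence from the 9.4% that the Introduction gives for Italy.** The target interval ends at 9%. The symmetric interval at n = 52 (4% ± 5.3 points) ends at about 9.3%. Both exclude 9.4%. The exact interval for 2/52 (0.5% to 13.2%) does include it, but its half-width is more than 5 points and no analysis of 52 children is planned. The 9.4% also refers to ages 6 to 9, not 2 to 18.
- **That the plan will report a negative lower limit, or is deficient for not naming an interval method.** The negative limit belongs to a symmetric interval, and the article names no method. That choice is commonly left to the analysis plan, which is not shown.

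**Conclusion.** The point holds as a minor correction. On the article's own inputs, 4% requires 59 to 60 children and not 52, while 52 requires about 3.5%. The discrepancy is 7 to 8 children (12% to 13%) in a component of the stated total. Separately, a 5-point half-width is an uninformative planning target for a 4% prevalence.

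The conclusion assumes the single-proportion formula with a two-sided 95% level and an absolute half-width, which the figure of 217 confirms. The precision quoted for 269 treats the children as independent and assumes prevalences near 17% and 4%. The evidence does not settle whether the 4% or the 52 should change. It does not show that 269 is too few for the prevalence aim, and it does not bear on whether 269 is enough for the regression models.

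**What to change.** 1. Check the cited prevalence source and reconcile the pair: either 4% with 59 to 60, or the unrounded prevalence (about 3.5%, if that is what the source gives) with 52.
2. Drop the addition of the two requirements. The same children supply both estimates, so the larger requirement, 217, governs. If only the 52 were replaced and the sum kept, the total would become 276 or 277 and would contradict the enrolment figure without need.
3. Keep the planned 269 and justify it by the precision it gives: about ±4.5 points at 17% and ±2.3 points at 4%, with an exact 95% interval of 2.1% to 7.2% if 11 of 269 children are obese. This replaces the 5-point target for obesity.

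The cost is a few lines of rewording in section 2.4. Enrolment, data collection and analysis are unchanged.

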### Study setting

2.1

To address FACILITY's purposes, 269 mother-child dyads will be consecutively enrolled at the paediatric outpatient clinic of the Buzzi Children's Hospital in Milan, Italy. The enrollment will last from February 2024 until December 2025.

Eligible dyads according to the following inclusion and exclusion criteria will be involved in the study.
-Inclusion criteria:
-For mothers: (i) age ≥18 years old, (ii) admission to the Department of Paediatrics, Buzzi Children's Hospital, (iii) ability to sign the informed consent.-For children/adolescents: (i) age between 2 and 18 years old, (ii) admission to the Department of Paediatrics, Buzzi Children's Hospital, (iii) informed consent signed by parents/local guardians.-Exclusion criteria:
-For mothers: (i) inability to understand the Italian and English language, (ii) refusal to sign the informed consent.-For children/adolescents: (i) presence of endocrine disorders (i.e., hypothyroidism, hypercortisolism, growth hormone deficiency), central nervous system damage (i.e., hypothalamic-pituitary damage because of surgery or trauma), genetic diseases either monogenic (i.e., leptin deficiency, MC4R mutation) or pleiotropic genetic syndromes (Prader-Willi, Bardet-Biedl), (ii) informed consent not written and signed by parents/local guardians.Moreover, if mothers return to the paediatric outpatient clinic with another child, the latter will also be enrolled if the inclusion criteria of the study are met. Written informed consent will be obtained from the parent or legal guardians. Variables will be collected by a trained research team (clinicians, registered dietitians, paediatricians, biologists).

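### The total of 269 is the sum of two sample sizes that the same children satisfy, and the 52 in that sum does not follow from 4%; the error is conservative and enrolment need not change

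*Protocol article*

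**What the plan says.** Section 2.4 (Data analysis) of the protocol article takes as its inputs "a prevalence of overweight and obesity in the target population of 17% and 4%, respectively". The criterion follows: "Considering a 95% level of confidence and 5% precision". From these it states that "217 individuals for overweight and 52 for obesity prevalence estimates are required, for a total sample size of 269 mother-child dyads".

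Section 2.1 (Study setting) describes one recruitment stream: "269 mother-child dyads will be consecutively enrolled at the paediatric outpatient clinic". It mentions no separate sample or stratum by weight status. The anthropometric paragraph of section 2.2 has height and weight taken for all children and classifies them by BMI Z-score: above 1 for overweight, 2 or more for obesity. Section 2.4 then says: "Prevalence of overweight and obesity will be estimated along with 95% confidence intervals".

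**The concern.** Two sample sizes may be added when they belong to two separate groups of people. Here each enrolled child is in the denominator of both proportions. One sample that serves two precision targets has to be as large as the more demanding target, and the other is then met as well. The printed total therefore cannot be what the stated criterion requires, although the text presents it so.

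The first study aim is to supply prevalence estimates for public health planning in the Milan area, so the link between sample size and precision is the main design statement for that aim. As written, it suggests that 52 children inform the obesity estimate, when all 269 do. One of the two components also does not come out of its own inputs.

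**Working it through.** **Inputs** (all from section 2.4): 95% confidence, so z = 1.96; precision d = 0.05, read as the absolute half-width of the interval; prevalences 17% and 4%; stated sizes 217, 52 and 269.

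**Formula for one proportion:** n = z² p(1 − p) / d², with z² = 3.8416 and d² = 0.0025.

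1. Overweight, p = 0.17: 3.8416 × 0.1411 / 0.0025 = 216.8, so 217. The plan's figure reproduces.
2. Obesity, p = 0.04: 3.8416 × 0.0384 / 0.0025 = 59.0 (59.007 unrounded), so 59 to 60. The plan's 52 does not reproduce.
3. Where 52 could come from:
   - p = 0.035 gives 3.8416 × 0.033775 / 0.0025 = 51.9, so 52. An unrounded prevalence near 3.5% would explain it.
   - z = 2 gives 61.4, and 90% confidence gives 41.6. Neither fits.
   - A finite-population correction that brings 59 to 52 needs a population of about 450. The same correction would cut 217 to about 147, so it was not applied to both.
4. Total: 217 + 52 = 269. The addition is correct as arithmetic and is the only route to 269 in the text.
5. Requirement for one sample with both prevalences at 17% and 4%: max(217, 60) = 217. The printed total exceeds it by 269/217 − 1 = 24%.

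**Dependence on the overweight definition.** A Z-score above 1 includes the obese children. Section 2.4 does not say whether the 17% includes the 4%. The Introduction quotes national figures as separate components (20.4% + 9.4% = 29.8%), so the exclusive reading of 17% is possible. Overweight as defined would then be 17% + 4% = 21%:

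- n = 3.8416 × 0.1659 / 0.0025 = 254.9, so 255.
- Excess of the printed total: 269/255 − 1 = 5%.

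**Precision with all 269 children in both estimates:** half-width = 1.96 × √(p(1 − p)/269).

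| Prevalence | Half-width | 95% interval |
|---|---|---|
| 17% | ±4.5 points | 12.5% to 21.5% |
| 21% | ±4.9 points | 16.1% to 25.9% |
| 4% | ±2.3 points | 1.7% to 6.3% |

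The normal approximation is rough at 4%, where about 11 obese children are expected (269 × 0.04 = 10.8). The Wilson interval there is 2.2% to 7.1%, a half-width of about 2.4 points, so the conclusion does not depend on the approximation.

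**The case against.** The strongest reply is that nothing is lost. The total exceeds either requirement, both estimates meet the 5-point target, and no estimate or model changes. The achieved intervals will be published with the results. This stands, and it limits the point to the justification of the number.

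A reader might infer more than the documents support:

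- **That the study is too small, or that the target must be changed.** Neither follows. The total lies above the requirement on both readings of overweight, and the documents give no reason to cut it.
- **That leaving out the expected half-widths at 269 is a fault in itself.** A protocol article commonly leaves this to the full protocol or analysis plan. It belongs in the correction only because the sentence has to be rewritten anyway.
- **That 217 certainly governs and 269 is 24% too large.** This holds only if overweight prevalence as defined is 17%. At 21% the excess is 5%.

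One defence would treat the extra 52 as an allowance for siblings, unusable records or the regression aim. The text does not offer this; it labels the 52 as the requirement for the obesity estimate. Another would read 217 and 52 as numbers of cases. That would need about 217/0.17 = 1,276 enrolled children, which contradicts section 2.1.

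**Conclusion.** The point holds as an invalid derivation with no shortfall. Because both prevalences are estimated in the same children, 269 does not follow from 95% confidence and 5-point precision. The requirement is the larger size: 217 at 17%, or 255 at 21%. Separately, 52 does not follow from 4%; the formula gives 59 to 60. That second error does not move the governing size, since overweight dominates either way.

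The conclusion that both estimates meet the target rests on the plan's assumed prevalences, on 5% meaning absolute points, and on 269 independent children with usable measurements. Section 2.1 allows further children of the same mother to be enrolled, and no allowance for this is included in the half-widths above. The room above the requirement is 269 − 217 = 52 children at 17%, but only 269 − 255 = 14 at 21%.

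The sponsor should fix this. It does not threaten the study.

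**What to change.** In section 2.4:

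- Delete the addition, and state that both prevalences are estimated in the whole sample.
- State that the overweight requirement governs, and say which case applies: 217 if overweight prevalence is 17%, or 255 if overweight is a Z-score above 1 including obesity and the 17% excludes the 4%.
- Correct either the 52 (to 59 or 60, if 4% is the intended input) or the 4% (if about 3.5% was used).
- Keep 269 and give the expected 95% half-widths: about ±4.5 points at 17% (or ±4.9 at 21%) and ±2.3 points at 4%.
- If there is a reason for enrolling above the requirement, state it explicitly. It has to be the sponsor's own, because the document contains none.

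The cost is a few sentences in the sample-size paragraph. Recruitment and data collection do not change, and the 269 in section 2.1 can stay.
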